## Assignment of interventions: blinding

### Who will be blinded {17a}

Evaluators of safety and efficacy outcomes including study clinicians and nursing staff, as well as study participants and their parents/guardians, are blinded to the randomization assignment for pediatric participants.

### Procedure for unblinding if needed {17b}

The study pharmacist maintains an unblinded version of the allocation sequence in a secure location for use in unblinding or for replacement should the original assigned envelope be damaged or lost. The pharmacist does not participate in other trial activities and will not share the list with study team members involved in participant follow-up activities. If circumstances arise where unblinding is needed before the end of the study (such as the occurrence of a suspected unexpected serious adverse reaction), the ISMs, who are physicians who are not investigators for this trial, will assess the child’s clinical status. Their report is shared with the sponsor and the DSMB. The DSMB then makes a recommendation for maintaining the blinding or unblinding which is communicated to the study sponsor.

## Data collection and management

### Plans for assessment and collection of outcomes {18a}

Trial data is collected by trained study staff, including clinical, safety, and outcome measures such as history, laboratory values, and neurological testing results. Data are collected onto paper-based CRFs and scanned into an electronic database.

### Plans to promote participant retention and complete follow-up {18b}

During informed consent, participants (or their parents/ guardians) are encouraged to adhere to the study follow-up visit schedule. A verbal map to their home and phone numbers is collected. A visit calendar with all study visit dates is affixed to each participant’s health passport book—a document carried to all health care visits in Malawi—to serve as a reminder. Participants who miss visits are contacted by phone and/or a home visit. Participants will have study team contact details and can contact investigators as the needed.

### Data management {19}

The study uses DF Explore—a 21 US Code of Federal Regulations Part 11-compliant internet data entry system provided by the study data coordinating center. The data system includes password protection and internal quality checks, such as automatic range checks to identify data that appear inconsistent, incomplete, or inaccurate. Data are first collected by study personnel on paper-based data collection forms that have the patient’s unique study identifier code on each page. The CRFs are then scanned into electronic CRFs (eCRF) on DF Explore and moved up 3 levels, with data verification at each level. All hard copy, research-related documents such as hard copy CRFs are stored securely in a locked office at the Ndirande Research Clinic (adults) or PRW (children). Only the study team members have access to these documents.

Study records and reports including, but not limited to, eCRFs, source documents, ICFs, laboratory test results, and study drug disposition records will be retained for 2 years after a marketing application is approved for DON for CM or, if no application is filed or if the application is not approved for DON, until 2 years after the investigation is discontinued and the US Food and Drug Administration (FDA) has been notified. These documents will be retained for a longer period of up to 5 years, however, if required by local regulations. ICFs documenting future use will be maintained as long as the specimens exist. No records will be destroyed without the sponsor’s written consent.

### Confidentiality {27}

No study information or associated data may be released to any unauthorized third party without prior written approval of DMID and the participant. Subject confidentiality will be maintained when results are disseminated. The study monitor or other authorized representatives of the sponsor or governmental regulatory agencies may inspect all documents and records, and the clinical study site will permit access to such records.

All hard copy records are kept locked. All computer entry and networking programs are carried out with participant code numbers and with password-protected systems. All non-clinical specimens, evaluation forms, reports, and other records that leave the site are identified only by a coded number. The sites hold a Certificate of Confidentiality which states that researchers cannot be forced to release information that may identify the research subject, even by a court subpoena, in any federal, state, or local civil, criminal, administrative, legislative, or other proceedings. The researchers may use the certificate to resist any demands for information that would identify the subject, except as explained above.

### Plans for collection, laboratory evaluation and storage of biological specimens for future genetic or molecular analyses {33}

This study does not include human genetic testing. Adult participants and parents/guardians of pediatric participants decide if their residual specimens can be used for future research or destroyed at the end of the trial. This decision may be changed at any time by notifying the study team. Residual specimens are stored indefinitely at the Kamuzu University of Health Sciences molecular biology laboratories or Laboratory of Immunogenetics (LIG) within NIAID. Specimens may be shared with other investigators upon written request to this study’s principal investigator. The recipients of specimens will be informed that these specimens have an NIH Certificate of Confidentiality. The information provided to a recipient will not contain direct identifiable information.

## Statistical methods

### Statistical methods for primary and secondary outcomes {20a}

The primary analysis is the comparison of the active doses against placebo in pediatric participants. For the dichotomous safety endpoints, unadjusted pairwise analyses use 95% confidence intervals of the difference in proportions between dose groups using Wilson score criteria. For the exploratory efficacy endpoints of cEEG amplitude or frequency, MRI brain volume score, age and sex standardized mean, and diastolic flow pattern for TCD, unadjusted pairwise analyses will calculate the 95% confidence interval of the mean difference of each endpoint’s first post-treatment measurement between dose groups using a *t*-statistic.

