Similarly, pediatric participants who fulfill enrollment criteria have pre-DON laboratory studies for safety and DON levels (Fig. 1B). Next, an IV line is placed, and participants receive IV fluids at standard maintenance rates. At enrollment, a lumbar puncture (LP) is performed both to rule out bacterial CNS co-infection and for DON mechanistic studies. IV artesunate is administered immediately upon confirmation of a CM diagnosis. Participants undergo a brain MRI (if available), TCD, and at least 30 min of EEG recording before administration of DON (or placebo). Participants remain hospitalized for a minimum of 24 h. Each pediatric participant is pre-medicated with ondansetron (0.15 mg/kg up to 5.0 mg) and receives DON IV or placebo at the pre-specified dose 30 min later. Ondansetron dosing is repeated at 8 and 16 h after DON administration. Due to the precariousness of CM and the young age of the pediatric participants, PK studies are employed through sparse sampling techniques at three of the following time points: 10 min, 30 min, 60 min, 90 min, and 3 h, 6 h, 12 h, and 18 h post-DON. A population PK analysis is used to estimate PK parameters in children. A repeat LP is performed 4 h after DON or placebo administration for metabolic studies. Participants remain hospitalized until their BCS is ≥ 3, they can drink unaided, and can sit with minimum assistance. Seven and 14 days after DON administration, blood samples for safety are obtained. At 1 and 6 months post-admission, surviving pediatric participants are examined for neurological sequelae and assigned a Glasgow Outcome Score (GOS-E) category.

Should any AEs or SAEs occur, they will be followed until resolution. During the 6-month enrollment period, should participants develop any clinical symptoms of concern, they are encouraged to return to visit study personnel for evaluation.

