### Sample size {14}

A sample size of 72 pediatric participants was chosen for logistical and feasibility reasons and is based on previous experience, both with respect to historical case numbers and ward infrastructure, with enrollments in similar phase I studies at the study site. We calculated the power to show certain effects with this sample size. The calculations for power to detect safety signals are from participants who received DON in the first 2 cohorts (*N* = 14), the first 3 cohorts (*N* = 28), and the first 4 cohorts (*N* = 56). The calculations for the exploratory efficacy endpoints use sample sizes of *N* = 36 (8 placebo vs. 28 DON) for the first half (cohorts 1, 2, and 3), and *N* = 72 (16 placebo vs. 56 DON) total enrollment. From those calculations, we see that the assumed effect sizes needed to have sufficient study power to ascertain differences between dosing groups are not unreasonably large. Most outcomes are measured within 7 days of enrollment during hospitalization. Adherence with 6-month follow-up visits was 85% in previous studies. Thus, we expect a very low attrition rate of up to 15% at the 6 months post-randomization visit. The goal of the pediatric study is to assess safety and explore a dose–response association for any safety or preliminary efficacy outcomes. We did not power the study to detect small effect sizes in any of the exploratory efficacy endpoints evaluated in the pediatric participants. Nevertheless, there is sufficient sample size to detect large effect sizes in continuous exploratory endpoints between two doses and placebo for a preliminary benefit-risk assessment before the fourth cohort of pediatric enrollments or for the final analysis.

For dichotomous (i.e., present/absent) safety endpoints, we calculate exact 90% central confidence intervals for the rate per participant, so that we are 95% confident that the rate is less than the upper limit. If the true rate for participants receiving DON is equal to an anticipated SAE background rate of 20%, then with a sample size of 14 participants receiving DON, we have over 85% power to show with 95% confidence that the true rate is not greater than 54%. Repeating those same calculations with sample sizes of 28 (and 56), we have over 85% power to show with 95% confidence that the rate is not greater than 46% (37%).

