### Interim analyses {21b}

After 50% of pediatric participants are enrolled, an interim analysis will assess the benefit-risk of the study drug to inform whether the study should continue. If a decision is made to continue, the dose–response relationship for both the primary safety endpoint and exploratory efficacy endpoints will inform which doses to study in the second half of pediatric enrollments.

For the exploratory efficacy endpoints of EEG amplitude or frequency, MRI brain volume score, and flow velocity on TCD, we will compare different dose groups using Welch’s *t*-test. We may use a linear regression dose response model to predict the effect size compared to placebo as a function of dose. For each exploratory efficacy outcome measured after DON administration, response may be modeled by dose group, or a more complicated model may be used such as a logit of area under the curve of the exposure profile, adjusting for disease severity at baseline.

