### Methods for additional analyses (e.g., subgroup analyses) {20b}

Exploratory analyses will compare DON doses to each other to assess preliminary efficacy. We will explore the impact of covariates including age, sex, and other characteristics (admission BCS, MRI brain volume score, serum glucose, serum lactate, cEEG, and/or admission TCD phenotype) by multivariable regression on the exploratory outcomes. In this multivariable model, dose will be either a categorical variable with fixed doses as categories or will account for PK of exposure measurements by using the area under the curve or *C*_max_ in the logistic regression. This adjusted model will only include characteristics that predict outcomes as determined by bivariate analyses.

For MRI brain volume scoring, GOS-E scoring, and TCD phenotype, which all rely on physician scoring, we will report Cohen’s Kappa measure on inter-rater reliability for outcomes evaluated by more than one physician. For endpoints measured multiple times during follow-up, sensitivity analyses will explore variation of these measurements over time in different groups by including random effects for time of measurement in the multivariable regression models.

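### The main efficacy comparisons use unadjusted post-dose EEG, TCD and MRI values; adjustment for the recorded pre-dose values is left to optional or data-selected models

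*Protocol article*

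**What the plan says.** **Main comparison.** Section {20a} of the protocol article covers the exploratory efficacy endpoints of EEG amplitude or frequency, MRI brain volume score and TCD flow. It says that "unadjusted pairwise analyses will calculate the 95% confidence interval of the mean difference", and the value compared is "each endpoint’s first post-treatment measurement between dose groups". No baseline term appears.

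**Interim.** Section {21b} says of the same markers that "we will compare different dose groups using Welch’s *t*-test". It adds that a more elaborate model may be used, "adjusting for disease severity at baseline". The interim results, with the safety results, inform the doses studied in cohort 4.

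**Pre-dose data.** The participant timeline {13} says: "Participants undergo a brain MRI (if available), TCD, and at least 30 min of EEG recording before administration of DON (or placebo"). The exploratory endpoints section likewise lists pre-dose EEG and TCD measurements and an admission MRI score.

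**Adjusted analysis.** Section {20b} plans a multivariable regression of the exploratory outcomes on age, sex and admission characteristics, which include the MRI score, cEEG and TCD phenotype. It then restricts the model: "This adjusted model will only include characteristics that predict outcomes as determined by bivariate analyses".

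**The concern.** The objectives {7} describe efficacy as change or improvement in these markers, and the abstract says that they are assessed before and after dosing. The comparison that the article puts first uses only the later value.

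At the interim each dose has 14 children and the pooled placebo group has 8. With groups that small, a difference in severity at entry can easily look like a drug effect or hide one. Using the pre-dose value of the same marker would reduce that risk and narrow the interval. As written, that happens only if the optional interim model is chosen, or if the data-driven screen in {20b} keeps the covariate. Standard errors from a model chosen that way also take no account of the selection.

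At stake is how well the interim look can separate a dose from placebo before the cohort 4 doses are settled.

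**Working it through.** **The plan's own figure.** Section {14} gives no numerical power for the efficacy endpoints, only the statement that large effects are detectable. Its safety power figures do reproduce. For example, with 14 children on DON and a true rate of 20%, up to 4 events give an exact one-sided 95% upper limit of 54.0%, with probability 87.0%.

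**Inputs from the article.**
- Interim: 14 children per dose and 8 pooled placebo ({11b}, {14}).
- Cohort 4: 36 children at 7:7:4, that is 14, 14 and 8 ({11a}).
- Final: 16 placebo and 56 DON ({14}). If a first-half dose is continued, that dose has 14 + 14 = 28 children against 8 + 8 = 16 placebo.

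**Assumption.** The correlation ρ between pre-dose and post-dose values is not given. I use 0.3, 0.5 and 0.7.

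**Method.** Two-sided 5% test, noncentral t distribution, equal SDs. The unadjusted standard error in SD units is √(1/n₁ + 1/n₂). ANCOVA on the pre-dose value multiplies it by √(1 − ρ²), which is 0.954, 0.866 or 0.714, and costs one degree of freedom.

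**Chance imbalance at the interim.** √(1/14 + 1/8) = 0.443. The probability of a baseline difference above 0.5 SD is 2 × [1 − Φ(0.5/0.443)] = 26%. An imbalance of 0.5 SD shifts the unadjusted difference by 0.5ρ, that is 0.15, 0.25 or 0.35 SD. At 28 against 16 the probability falls to 11%.

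**Difference detectable with 80% power (SD units).**

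| Comparison | Unadjusted | ρ = 0.3 | ρ = 0.5 | ρ = 0.7 |
|---|---|---|---|---|
| Interim, 14 v 8 | 1.31 | 1.25 | 1.13 | 0.93 |
| Final, 28 v 16 | 0.90 | 0.86 | 0.78 | 0.64 |
| Final, 56 v 16 | 0.81 | 0.77 | 0.70 | 0.58 |

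**Power for a 1 SD difference, interim 14 v 8.** 57% unadjusted; 61%, 70% and 85% adjusted.

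**Effect of adding cohort to the interim model.** At that point 0.1 mg/kg has been given only in cohorts 1 and 2 and 1.0 mg/kg only in cohort 3. Each of these two strata has 4 placebo children. With a stratum term, each dose is compared with its own 4 controls, and the standard error factor becomes √(1/14 + 1/4) = 0.567. With residual variance pooled over all 36 children (36 − 5 = 31 degrees of freedom), the detectable difference is 1.42, 1.31 and 1.17 SD at ρ = 0.5, 0.6 and 0.7. The unadjusted pooled-placebo figure is 1.31. The cohort term therefore cancels most of the gain from the baseline term.

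**The bivariate screen.** The article gives no threshold. If it is p < 0.05 with 36 children, the marker's own baseline is kept in about 43% of trials at ρ = 0.3, 89% at 0.5, 98% at 0.6 and over 99% at 0.7.

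**The case against.** The case for leaving the plan alone has several sound parts.

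- **Adjustment is planned.** A reader might infer that the baseline is thrown away and imbalance never addressed. The article does not support that: {20b} regresses the outcomes on the admission markers, and {21b} allows a model with baseline severity. Presenting the unadjusted result first and the adjusted one second is a common layout. The remaining fault is that the adjustment is neither fixed in advance nor part of the main comparison.
- **The unadjusted test is not invalid.** A reader might infer bias. Under randomisation the difference is unbiased, and its standard error already allows for chance imbalance.
- **The screen mostly keeps a useful baseline.** At ρ of 0.5 or more it would rarely drop it. It is likely to drop it only near 0.3, where adjustment gains little. It still makes the model depend on the data and leaves standard errors that ignore the selection.
- **Scope.** Groups of 8 to 14 describe the interim only. Seizure minutes are counted only after dosing and have no pre-dose value, and MRI depends on availability. The article does not say that baseline severity is the strongest predictor of the post-dose value. It calls the markers prognostic for mortality, which is a different statement.
- **Consequence.** The endpoints are exploratory. Cohort 4 dosing also rests on safety, pharmacokinetics, adult data and regulatory review, and no efficacy test acts as a decision rule.

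These points limit the concern to precision and prespecification. None gives a reason to leave an available pre-dose value out of the main comparison.

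**Conclusion.** The point holds as an improvement that needs no new data, not as an error that invalidates the analysis. The comparisons that the article puts first, at the interim and at the end, leave out pre-dose values of the same markers, and the adjustment offered elsewhere is optional or selected from the data.

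The size depends on the assumed correlation. At the interim the gain is small at 0.3 (1.31 to 1.25 SD) and material at 0.5 to 0.7 (1.13 to 0.93 SD). At the final analysis with 28 against 16, the detectable difference falls from 0.90 to 0.86, 0.78 or 0.64 SD.

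The interim figures pool placebo children across cohorts, as {14} does. Half of those 8 were not randomised alongside the dose in question, so the pooled contrast also assumes no drift between cohorts.

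**What to change.** 1. In {20a} and {21b}, for each continuous marker with a pre-dose measurement, make ANCOVA the main comparison: first post-dose value on dose group, with that marker's own pre-dose value as a fixed covariate.
2. In {20b}, replace the bivariate screen with a short covariate list named in advance, for example the marker's baseline value, age and admission BCS.
3. Keep the unadjusted difference and its interval as supportive.
4. Do not put cohort in the main interim model. Report a model with cohort as a sensitivity analysis, to show whether pooling placebo across cohorts matters.
5. Say how a child without a pre-dose MRI is handled; {20c} already allows multiple imputation.

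The cost is a change of wording and one degree of freedom for the baseline term. No further measurements are needed.

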### Interim analyses {21b}

After 50% of pediatric participants are enrolled, an interim analysis will assess the benefit-risk of the study drug to inform whether the study should continue. If a decision is made to continue, the dose–response relationship for both the primary safety endpoint and exploratory efficacy endpoints will inform which doses to study in the second half of pediatric enrollments.

For the exploratory efficacy endpoints of EEG amplitude or frequency, MRI brain volume score, and flow velocity on TCD, we will compare different dose groups using Welch’s *t*-test. We may use a linear regression dose response model to predict the effect size compared to placebo as a function of dose. For each exploratory efficacy outcome measured after DON administration, response may be modeled by dose group, or a more complicated model may be used such as a logit of area under the curve of the exposure profile, adjusting for disease severity at baseline.

### Methods for additional analyses (e.g., subgroup analyses) {20b}

Exploratory analyses will compare DON doses to each other to assess preliminary efficacy. We will explore the impact of covariates including age, sex, and other characteristics (admission BCS, MRI brain volume score, serum glucose, serum lactate, cEEG, and/or admission TCD phenotype) by multivariable regression on the exploratory outcomes. In this multivariable model, dose will be either a categorical variable with fixed doses as categories or will account for PK of exposure measurements by using the area under the curve or *C*_max_ in the logistic regression. This adjusted model will only include characteristics that predict outcomes as determined by bivariate analyses.

For MRI brain volume scoring, GOS-E scoring, and TCD phenotype, which all rely on physician scoring, we will report Cohen’s Kappa measure on inter-rater reliability for outcomes evaluated by more than one physician. For endpoints measured multiple times during follow-up, sensitivity analyses will explore variation of these measurements over time in different groups by including random effects for time of measurement in the multivariable regression models.

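### Screening covariates against the outcome biases the exploratory adjusted dose effect modestly toward zero; a short pre-specified covariate set would avoid this

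*Protocol article*

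**What the plan says.** The rule stands in the protocol article, in the section on methods for additional analyses {20b}. The purpose given is exploratory: "We will explore the impact of covariates including age, sex, and other characteristics". Besides age and sex, the named candidates are "admission BCS, MRI brain volume score, serum glucose, serum lactate, cEEG, and/or admission TCD phenotype", which makes eight in all. Dose enters the same multivariable model, either as categories or through exposure. The section then fixes how covariates are chosen: "This adjusted model will only include characteristics that predict outcomes as determined by bivariate analyses". No candidate is protected from the screen, not even the endpoint's own pre-dose value, although EEG, TCD and (where available) MRI are recorded before dosing.

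Three other places set the context:
- The section on primary and secondary outcomes {20a} makes the main efficacy comparisons unadjusted confidence intervals for mean differences.
- The interim section {21b} says of the efficacy endpoints that "we will compare different dose groups using Welch’s *t*-test". It also allows, as an option, a model adjusted for baseline disease severity, and mentions no bivariate screen.
- The sample size section {14} bases the efficacy calculations on "sample sizes of *N* = 36 (8 placebo vs. 28 DON) for the first half (cohorts 1, 2, and 3"), and on 16 placebo and 56 DON children at full enrolment.

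**The concern.** A covariate is useful in a dose model if it predicts outcome within arms. The stated screen looks instead at its association with outcome across all children, and with a real dose effect that association mixes two things: the within-arm relation and any chance imbalance between arms. Imbalance in the direction of the drug effect raises the apparent association, so the covariate is kept and its share of the difference is taken out. Imbalance in the other direction lowers the association, so the covariate tends to be dropped and nothing is given back. The errors do not cancel, and the average adjusted estimate falls short of the truth.

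The screen can also drop real predictors in a small sample, and can give each endpoint and each analysis a different covariate set. At stake are the size and interpretability of the adjusted dose effect, the one adjusted estimate the article commits to rather than merely permits.

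**Working it through.** **What can be reproduced.** The article gives no efficacy power figure, effect size, SD or covariate correlation. Its only numerical power statements concern safety, and they reproduce with exact 90% intervals at a true rate of 20%:
- n = 14: at most 4 events, upper limit 0.540, power 87.0%.
- n = 28: at most 8 events, upper limit 0.457, power 91.0%.
- n = 56: at most 14 events, upper limit 0.363, power 86.4%.

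They say nothing about the adjusted model, so what follows rests on stated assumptions.

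**Mechanism, one covariate.** Take 8 placebo and 28 DON children, a true effect of 0.8 SD, unit within-arm variances and a within-arm correlation of 0.3. One standard error of chance imbalance is √(1/8 + 1/28) = 0.40 SD. The total cross-product is 34 × 0.3 + (8 × 28/36) × ΔX × ΔY, where 34 is the within-arm degrees of freedom, 8 × 28/36 = 6.22, and ΔY = 0.8 + 0.3 × ΔX.

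- ΔX = +0.4: ΔY = 0.92. Cross-product 10.2 + 6.22 × 0.4 × 0.92 = 12.49. Sums of squares 34 + 6.22 × 0.16 = 35.0 and 34 + 6.22 × 0.92² = 39.3. Correlation 12.49/√(35.0 × 39.3) = 0.337.
- ΔX = −0.4: ΔY = 0.68. Cross-product 10.2 − 6.22 × 0.4 × 0.68 = 8.51. Sums of squares 35.0 and 36.9. Correlation 8.51/√(35.0 × 36.9) = 0.237.

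Significance at p < 0.05 with n = 36 needs a correlation of 2.032/√(34 + 2.032²) = 0.329. The first covariate passes and the estimate is corrected from 0.92 to 0.80. Its mirror image fails and the estimate stays at 0.68. The average of this pair is (0.80 + 0.68)/2 = 0.74 against a truth of 0.80. Always adjusting gives 0.80, and so, on average, does never adjusting.

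**Simulation.** Eight independent normal covariates, linear model, two-sided 5% test, 2,500 to 3,000 replicates per scenario (Monte Carlo error about √(0.25/2,500) = 1 point of power). Thresholds of 0.05, 0.10 and 0.20 were tried, with true effects of 0.8, 1.0 and 1.2 SD at N = 36 and 0.8 SD at N = 72. Selected rows, effect 0.8 SD, threshold 0.05:

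| Placebo vs DON | Prognostic correlations | Bias, screened | Unadjusted power | All eight | Fixed prognostic set | Screened |
|---|---|---|---|---|---|---|
| 8 vs 28 | 0.7 | −2.3% | 48.1% | 64.6% | 74.4% | 73.2% |
| 8 vs 28 | 0.5, 0.3 | −5.8% | 51.2% | 55.7% | 65.0% | 59.4% |
| 8 vs 28 | four at 0.3 | −8.8% | 48.0% | 55.3% | 62.2% | 51.4% |
| 16 vs 56 | 0.7 | −1.1% | 78.1% | 95.7% | 97.6% | 97.4% |
| 16 vs 56 | 0.5, 0.3 | −2.2% | 79.7% | 89.6% | 92.6% | 91.0% |
| 16 vs 56 | four at 0.3 | −4.8% | 80.3% | 90.8% | 92.5% | 88.0% |

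Across the main scenarios:
- **Bias:** about 2-10% low at 8 vs 28, 5-16% low for one dose (14) against placebo (8), and 1-5% low at 16 vs 56. With all eight covariates at 0.3 the first two reach about 15% and 19%.
- **No true effect:** no bias; type I error about 4.4-5.6%.
- **Power loss against a fixed, truly prognostic set:** about 1-11 points at 8 vs 28 (31 in the extreme case) and 0-5 at 16 vs 56.

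**Baseline-only comparison.** Arms 8/14/14, top-dose effect 0.8 SD, the endpoint's baseline correlated 0.6 or 0.4 with outcome, two others at 0.3 and five null. The screened model gives mean estimates of 0.75 or 0.74 and power of 60% or 46%. Fixing the baseline value alone gives 59% or 47% without the bias. Fixing all three prognostic covariates gives an estimate of 0.80 and power of 69% or 54%. With arms 16/28/28 the screened model has somewhat more power than baseline alone. Where the baseline is the only prognostic covariate, fixing it is the better choice, as in the 0.7 rows.

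**The case against.** The strongest case against is that little depends on this model. It is exploratory, the committed efficacy comparisons are unadjusted, and the article says the study was not powered for small efficacy effects. All of that stands and limits the point.

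A reader might infer that the rule costs a definite amount of power at the interim, where cohort 4 doses are informed. The documents do not support this. The interim section specifies Welch's t-test, and its optional severity-adjusted model carries no screen. The N = 36 results show only what would happen if the screened model were fitted then.

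Nor can a single figure for the power loss be defended. It depends on unstated correlations, effect size and threshold, and on a comparator that holds exactly the prognostic covariates, which nobody knows in advance. Screening usually has more power than the unadjusted test (59.4% against 51.2% in one row). When no covariate is prognostic it has 7-10 points more than a model with all eight.

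The bias is also small beside sampling error: 0.05-0.06 SD against √(1/8 + 1/14) = 0.44 SD, and about 0.02 SD against √(1/16 + 1/28) = 0.31 SD with full enrolment. It would be wrong, too, to say that the screen mostly lets noise in. At N = 36 the baseline value is kept 96% or 65% of the time in the baseline-only comparison, while each null covariate enters 5% of the time. Covariates with a correlation of 0.3 are kept only about 40% of the time.

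One argument does not hold: that this is detail left to an analysis plan. The selection rule is stated in the article; only the threshold and final list could be elsewhere.

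**Conclusion.** The point holds as a modest one about a single exploratory model. The direction of the bias follows from the method and appeared in every simulated scenario with a true effect. Its size is an assumption-dependent range: roughly 2-10% at N = 36, up to about 16% for a single dose against placebo, and about 1-5% at N = 72.

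False positives are not inflated. The power cost is uncertain: about 1-11 points at N = 36 and 0-5 at N = 72 against a fixed set that is truly prognostic. Against baseline-only adjustment there is none, or a small gain from screening, where other candidates are also prognostic. The case for change therefore rests on an unbiased estimate and the same covariates at each analysis, more than on power. The stated interim test and the main unadjusted comparisons are unaffected.

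**What to change.** Replace the selection sentence in section {20b} with a covariate set fixed before any unblinded look and used at every analysis in which the adjusted model is fitted: the endpoint's own pre-dose value, plus at most two named admission severity variables from the existing list (BCS and lactate are examples; the choice is the trial team's). Report bivariate associations in a descriptive table that does not decide model content.

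The cost is one sentence in the protocol and its counterpart in any analysis plan. The downside is one or two degrees of freedom, and slightly lower power, if a named covariate proves not to be prognostic.
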